## Abstract

**Background:**

Stroke has a considerable socio-economic impact worldwide and is the leading cause of disabilities in the Western world. Economic studies of stroke focus merely on physical aspects and clinical interventions. To our current knowledge there is no comprehensive economic study investigating the economic impact of stroke including psychological and social aspects. The €-Restore4Stroke project, part of a large comprehensive research programme Restore4Stroke, aims to investigate the total economic impact of stroke in the Netherlands.

**Methods:**

Two trial-based economic evaluation studies will be conducted within the €-Restore4Stroke project: one focussing on a self-management intervention and one on an augmented cognitive behavioural therapy intervention. Both include cost-effectiveness analyses and cost-utility analyses as primary research methods. Furthermore, a cost-of-illness study investigating costs after stroke attached to a cohort study and a record linkage study in which four databases are linked to investigate patterns of health care consumption before and after stroke, are embedded in €-Restore4Stroke. All studies will be performed from a societal perspective. The primary outcome measure for the cost-effectiveness analysis is the increase in health status on the primary outcome scales. Within the cost-utility analysis, the primary outcome measure is quality-adjusted life years (QALYs) for which an indirect preference-based technique will be used. In the self-management study we will also look at the estimation of health effects on informal caregivers. Cost outcomes in the cost-of-illness study will be computed with a cost questionnaire and linkage of several databases will be used to derive outcomes in the record linkage study,

**Discussion:**

€-Restore4Stroke will provide new insights and evidence for the economic impact of psychosocial consequences after stroke. Besides being innovative in various ways (i.e. focussing on the chronic phase after stroke and including personal factors as possible determinants of long-term re-integration including quality of life in a prospective longitudinal design), a major strength of €-Restore4Stroke is that we include impact on informal caregivers. The outcomes of this study will provide health care decision makers with valuable and necessary information regarding stroke care related decisions.

**Trial registration:**

NTR3051 (RCT Self-management), NTR2999 (RCT Augmented Cognitive Behavioural Therapy)

## Background

Stroke has a major socio-economic impact worldwide and is the leading cause of disabilities in the Western world. It is estimated that the worldwide prevalence of stroke is 0.2% of the world population. Of the people who suffer from a stroke, 30% die, 30% are left functionally disabled and 40% have a successful recovery with minor to no disabilities [1]. It is estimated that by 2023 the absolute number of patients experiencing a first stroke will increase, in comparison with 1983, by 30% worldwide [2]. The disease impact of stroke is considerable on stroke patients and on their informal caregivers. More than 50% of the stroke survivors return to their homes after being discharged from the hospital [3]. At home, these survivors and their informal caregivers have to deal with the long term consequences of stroke, which are seen in physical, psychological and social areas of functioning [4,5].

Not only the clinical, but also the financial burden of stroke is considerable [6]. Currently, approximately 3-4% of total health care expenditures in Western countries are spent on stroke [7]. On the one hand, governments are cutting down on expenditures for health care, while on the other hand the health care sector is facing an increased demand for stroke care, due to demographic changes (e.g. an aging population) and changing attitudes towards health care (e.g. more demanding society; value for money) [8]. The growing demand for stroke care and the limited resources available for health care, have led to an increased interest in the economic aspects of stroke. The last few years have shown a remarkable increase in the publication of economic studies on stroke [7]. A Pubmed search combining "Cerebrovascular disorders" and "Costs and cost-analysis" shows that since 1990 the number of stroke studies including costs have increased in both absolute and relative terms. Figure 1 shows this development from 1990 until 2010, the last year for which complete data were available.

**Figure 1 F1:**
[figure not shown]
**Development publications on cost analysis and cerebrovascular disorder studies**.

In general, these economic studies of stroke focus primarily on physical aspects and clinical care [9-14]. It is known that recovery from stroke also depends on psychological and social aspects. To our current knowledge there is no comprehensive economic study that investigates the economic impact of stroke including psychological and social aspects. This article presents the design and methods of a study which aims on investigating and determining the economics of psychosocial care after stroke. The present study, €-Restore4Stroke (pronounce as e-Restore), is part of a Dutch national consortium called Restore4Stroke. Within Restore4Stroke, four large studies are executed aiming to improve the quality of life of stroke patients and the concurrent effects on their informal caregivers. Three of these studies focus more on outcomes while the fourth, €-Restore4Stroke, is designed, among other things, to investigate the economic aspects of the other three studies.

### Restore4Stroke

In addition to €-Restore4Stroke, the following three studies are embedded in Restore4Stroke: two randomized controlled trials (RCTs) and a cohort study. The first RCT, Restore4Stroke Self-Management (referred to as Self-Management study), aims at enhancing self-management in stroke patients and their informal caregivers. The second RCT, Restore4Stroke Augmented Cognitive Behavioural Therapy (referred to as the Augmented CBT study), aims at decreasing depression and anxiety complaints in stroke patients. With the third study, the Restore4Stroke Cohort study (referred to as the Cohort study), the course of quality of life in stroke patients and their informal caregivers is investigated, and factors predicting quality of life, including pre-stroke health situation factors, stroke-related factors, personal factors and partner factors are determined. In this design article we will focus on the economic aspects of all four studies, for further details on the other aspects of the two RCTs and the cohort we refer to publication elsewhere.

For current status updates you can also visit http://www.restore4stroke.nl.

All studies described in this article are approved by a legally recognized medical ethics committee. The Self-Management study was approved by the Medical Ethics Committee Utrecht Medical Center. The Augmented CBT study was approved by the Committee On Research involving Human Subjects (CMO) Arnhem/Nijmegen. The Cohort study was approved by the Committee Research involving Human Subjects (CMO) St. Antoniusziekenhuis, Nieuwegein. All ethics approval committees are located in The Netherlands.

### €-Restore4Stroke

The €-Restore4Stroke project consists of four sub-studies. Attached to both RCTs, an economic evaluation study will be performed. Economic evaluation studies compare two or more health care interventions and investigate the relationship between costs and effects. Furthermore, a cost-of-illness study will be performed for the Restore4Stroke cohort. Cost-of-Illness studies aim at determining the total costs of a disease for society. Finally, the fourth sub-study within €-Restore4Stroke is a record linkage study. In this study, we will focus on changes in health care consumption 5 years before and 5 years after stroke through register and database linkage. An overview of all four studies is provided in Figure 2.

**Figure 2 F2:**
[figure not shown]
**Overview Restore4Stroke**.

## Methods

### Aim and research questions

The overall €-Restore4Stroke aim is to fully capture the economic impact of psychosocial care after stroke. Looking at the 4 subprojects embedded in this study, the following research questions will be answered:

• From a societal perspective, what are the costs and effects of the Self-Management intervention in comparison with an education intervention?

• From a societal perspective, what are the costs and effects of the Augmented CBT intervention in comparison with a computerized cognitive training intervention?

• How do patterns of care received after stroke (in terms of health care costs, productivity costs, costs of informal care) change during the time of the follow-up period of the Cohort study and what is their impact on the patient (in terms of health-related quality of life, life satisfaction and emotional functioning) in economic terms as well?

• How do patterns of health care consumption after stroke (in terms of health care costs, productivity costs, costs of informal care) change during the 5 years after stroke, in comparison with the 5 years before stroke and what is the economic impact of these changes from a societal perspective (record linkage study)?

### €-Restore4Stroke outcome measures

All studies included in the €-Restore4Stroke project will be performed from a societal perspective meaning that all costs and outcomes of both the interventions and comparators will be included. Within the Restore4Stroke programme, Quality of life (QOL) is considered both from a general Health-Related Quality Of Life (HRQOL) and domain-specific QOL perspective. The general HRQOL perspective is operationalised as disease-specific HRQOL measured with the Stroke Specific Quality of Life (SS-QoL [15]), and generic HRQOL measured with the 5-dimensional EuroQol (EQ-5D [16]). The domain-specific perspective consists of the domains: participation measured with the Utrecht Scale for Evaluation and Revalidation Participation (*Utrechtse Schaal voor Evaluatie en revalidatie - Participatie *or USER-p [17]), emotional functioning measured with the Hospital Anxiety and Depression Scale (HADS [18]) and subjective well-being measured with 3 satisfaction questions. An overview of the primary and secondary outcome measures of all studies embedded in the Restore4Stroke programme is presented in Table 1.

**Table 1 T1:** Outcome measures Restore4Stroke (x: cost questionnaires, p: primary outcome measure, s: secondary outcome measure)

	Self-Management study				Augmented CBT study				Cohort study				
	T0	T1	T2	T3	T0	T1	T2	T3	T1	T2	T3	T4	T5

***Primary outcomes €-Restore4Stroke***													

Cost Questionnaire	x	x	x	x	x	x	x	x		x^a^	x^a^	x^a^	x^a^

CarerQol Questionnaire	s	s	s	s									

***Primary outcomes Restore4Stroke***													

EQ-5D^b^	s	s	s	s	s	s	s	s		s	s	s	s

HADS^c^	s	s		s	p	p	p	p	s	s	s	s	s

USER-P^d^	s	s		s	s	s	s	s	p	p	p	p	p

SS-Qol-12^e^	s	s		s	s	s	s	s		s	s	s	s

Life satisfaction	s	s		s	s	s	s	s		s	s	s	s

***Other outcomes***													

UPCC^f^	p	p	p	p									

VAS^g^	s	s		s									

ECSI^h^	s	s		s									

PSDRS^i^					s	s	s	s					

GSES^j^	p	p	p	p									

GAS^k^					s	s	s	s					

^a^The cost questionnaire used in the cohort study is a short questionnaire (11 items) compared to the cost questionnaire used in the Self-Management and augmented CBT Study (19 items)

^b^5 Dimensional EuroQol

^c^Hospital Anxiety and Depression Scale

^d^Utrecht Scale for Evaluation and Regabilitation Participation (*Utrechtse Schaal voor Evaluatie en Revalidatie - Participatie*)

^e^Stroke Specific Quality of Life

^f^Utrecht Proactive Coping Competence list

^g^Visual Analogue Scale

^h^Expanded Caregiver Strain Index

^i^Post Stroke Depression Rating Scale

^j^General Self-Efficacy Scale

^k^Goal Attainment Scale

### Designs

The study design is distinctive for each study and will be explained in the following section.

#### Self-Management study and Augmented CBT study

Both trial-based economic evaluations will involve a combination of a cost-effectiveness analysis (CEA) and a cost-utility analysis (CUA). Costs will be calculated in various ways. Effects will be presented as clinical outcomes, which are the primary outcome parameters of both the Self-Management study (i.e. the UPCC) and the Augmented CBT study (i.e. the HADS). In a CUA, costs are calculated in a similar way as in a CEA, but effects are usually expressed in quality-adjusted life years (QALYs) [19]. A QALY combines two distinct variables: quality or utility (the value which stroke patients attach to their current health status) and quantity (life years gained) of health. Utilities in both studies will be derived from the Five-Dimensional Euroqol (EQ-5D). The EQ-5D is chosen because it is a widely used quality of life instrument, also in the field of stroke. To estimate the incremental cost-effectiveness, the incremental cost-effectiveness ratio (ICER) will be calculated for both the CEA and CUA. If there are two alternative interventions, their difference in cost (incremental cost) is compared with their difference in outcomes (incremental effect) by dividing the former by the latter. This ratio is known as the ICER and is expressed as the incremental cost per point improvement on the primary outcome measure or otherwise costs per QALY.

In addition, in the Self-Management study we will include a questionnaire to investigate the quality of life of informal caregivers. Performing an economic evaluation from a societal perspective means including all relevant costs and effects, but economic evaluations of health care interventions usually treat patients as isolated individuals in determining the relevant health effects. Consequently, the quality of life of informal care is usually neglected in these studies. To address this issue, the CarerQOL [20] questionnaire will be included in the Self-Management study.

### Sample size calculation

The sample size calculation of the Self-Management study is based on a method presented by Jones et al. [21]. Based on two earlier intervention studies with the UPCC [22,23], a standardised difference was calculated representing the difference between the means/population standard deviation. The studies resulted in two different outcomes: a difference in means of .2 and .3 respectively between the groups on the UPCC and a mean SD of .35 and 0.6 respectively. Based on these studies, a standardised difference of .6 on the UPCC was used for the power calculation (.2/.35 = .57). Based on the method of Jones et al, 45 patients per group are needed based on an alpha of .5 and a power of 80%. Assuming a drop-out rate of 15%, 106 patients (2 × 53) will be recruited for this study.

Based on previous research, it has not been possible to conduct a power calculation on the HADS as the psychological intervention studies in the Cochrane review [24] all used different outcome measures and not the HADS. Hence, the sample size calculation for the Augmented CBT study will be based on other measures and is therefore identical to the sample size calculation for the Self-Management study (2 × 53 = 106).

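### Sample size: alpha is misprinted as .5, the 80% power holds only at d = .6 (above both cited source effects of .57 and .50), and the 106 taken over for the CBT trial has no stated HADS basis

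*Protocol article*

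**What the plan says.** Everything is in the first Sample size calculation section of the protocol article, which covers both randomised trials.

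- **Source data.** Two earlier UPCC intervention studies are reported as showing "a difference in means of .2 and .3 respectively between the groups on the UPCC", with "a mean SD of .35 and 0.6 respectively".
- **Planning effect.** From these, "a standardised difference of .6 on the UPCC was used for the power calculation (.2/.35 = .57"). The corresponding ratio for the second study is not worked out.
- **Error rates and size.** The text then states that "45 patients per group are needed based on an alpha of .5 and a power of 80" per cent. It does not say whether the test is one- or two-sided.
- **Drop-out.** "Assuming a drop-out rate of 15%, 106 patients (2 × 53) will be recruited".
- **Augmented CBT trial.** The article says that a HADS power calculation was not possible, because the earlier psychological intervention studies used other instruments. It continues that "the sample size calculation for the Augmented CBT study will be based on other measures and is therefore identical" to the Self-Management one, again 2 × 53 = 106.

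Two other places bear on this. Designs (Self-Management study and Augmented CBT study) names the HADS as the CBT trial's primary outcome, and Table 1 lists the UPCC under the Self-Management study only. Statistical analysis says that the power of both trial-based economic evaluations rests on the trials.

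**The concern.** Three figures in this one paragraph do not sit well together.

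1. The printed type I error is ten times the usual one and does not lead to the printed group size. A reader cannot tell from the text which of the two is wrong, or which sidedness was meant.
2. The planning effect is presented as based on two studies, yet it exceeds what either of them gives. The stated power therefore applies to an effect that neither source reports.
3. The CBT trial's size comes from an effect on a coping scale that Table 1 does not list for that trial, while its primary outcome is a mood scale.

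The UPCC and the HADS are also the effect measures of the two cost-effectiveness analyses, so this paragraph is the only sizing rationale in the article for both trials and both evaluations. If the Self-Management trial shows no clear UPCC effect, the result would be read against a 20% chance of missing a real one. At the lower source effect that chance is about 35%.

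**Working it through.** **Inputs, all from the Sample size calculation section:** power .80; printed alpha .5; planning effect d = .6; source studies .2 with SD .35 and .3 with SD .6; 1:1 allocation; drop-out 15%.

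**Formulas.** Normal approximation: n per group = 2(z₁₋α/₂ + z₁₋β)²/d². Power = Φ(d√(n/2) − z₁₋α/₂). Each result was also computed with the noncentral t distribution; those values are marked (t). Patients are treated as independent.

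**Step 1: reproduce the plan's 45 and 106.**
- α = .05 two-sided, d = .6: 2(1.960 + 0.842)²/.36 = 15.70/.36 = 43.6, so 44; (t) 44.6, so **45**.
- Power at 45 per group: √(45/2) = 4.743; .6 × 4.743 − 1.960 = 0.886, so 81.2%; (t) **80.4%**.
- Drop-out: 45/.85 = 52.9, so 53; 2 × 53 = **106**.

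The stated size and power both reproduce.

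**Step 2: try the printed alpha and the other sidedness.**
- α = .5 two-sided, d = .6: 2(0.674 + 0.842)²/.36 = 12.8, so 13; (t) 11.9, so **12**. At 45 per group, power would be 98.5%.
- α = .5 one-sided, d = .6: 4 per group.
- α = .05 one-sided, d = .6: (t) 35.04, so 36.

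Of the combinations tried, only two-sided .05 leads to 45.

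**Step 3: the source effects.** .2/.35 = .571 and .3/.6 = .50. Both are below .6.

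**Step 4: power with 45 analysed per group, and the size needed for 80%, α = .05 two-sided (t).**

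| d | Power at 45 per group | n per group for 80% | Recruited at 15% drop-out |
|---|---|---|---|
| .60 (planned) | 80.4% | 45 | 53 per group, 106 |
| .571 (first study) | 76.5% | 50 | 50/.85 = 58.8, so 59; 118 |
| .50 (second study) | 65.0% | 64 | 64/.85 = 75.3, so 76; 152 |

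The normal approximation gives powers of 81.2%, 77.4% and 66.0%. If no one dropped out and all 53 per group were analysed, power (t) would be 83.0% at .571 and 72.2% at .50.

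**Step 5: the CBT trial.** The article gives no HADS difference and no HADS SD, so power on the HADS in points cannot be computed from it. What follows from the size alone is the line for d = .60: 45 analysed per group detects a difference of 0.6 SD with 80% power on any continuous outcome, the HADS included.

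**The case against.** The strongest reply is that the calculation works. Once alpha is read as .05 two-sided, the declared d = .6 gives 45 per group, 80% power and 106. This stands. A reader might infer that the trial was planned with a 50% false-positive rate, or that the stated power cannot be obtained at all. Neither is supported: the group size itself shows that .05 was used, and the slip changes neither size nor power.

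A second reply is that choosing a planning effect is a judgement, made here in full view: .57 is printed beside .6, and the second study's figures are given. Rounding .57 to .6 costs about 4 points of power, or 5 patients per group, and Setting and participants calls 106 a minimum. This stands in part. It is an optimistic assumption, not an arithmetic error. But the text says that it rests on both studies, and the second gives .50, at which power is about 65%. Even with no drop-out, 106 gives only about 72% there.

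Third, a reader might infer that the article claims 80% power on the HADS, or that the CBT trial is underpowered. It makes no such claim and says that no HADS calculation could be done. Without a HADS effect or SD, its power on that scale cannot be shown to be too low. What remains is that lacking HADS data is no reason for a UPCC effect to carry over.

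Finally, the uncertainty of the cost-effectiveness ratio is handled by bootstrapping, acceptability curves and sensitivity analysis, not by a powered test. The consequence for the economic results is therefore smaller than for the clinical outcomes.

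**Conclusion.** The point holds in a limited form.

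- **Alpha** is misprinted. The 45 per group corresponds to .05 two-sided; .5 would need about 12.
- **Power** of 80% in the Self-Management trial holds only at d = .6, above both source effects. With 45 analysed per group it is about 76% at .57 and about 65% at .50.
- **The CBT trial's 106** has no stated basis on the HADS. This is an unsupported figure, not one shown to be wrong.

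It does not follow that 106 is invalid or that more patients must be recruited; the number is consistent with the effect that the plan declares.

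The power figures assume a two-sample comparison of means, 15% drop-out and independent patients. Both Self-Management arms are delivered in group sessions (Interventions), so any correlation within groups would lower real power below these figures. The article gives no value from which to say by how much.

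**What to change.** In the Sample size calculation section:

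1. Replace the printed alpha with .05, two-sided.
2. Keep 45 analysed and 53 recruited per group (106). State the power as 80% at a standardised difference of .6, about 76% at .57 and about 65% at .50, and say that .6 is above both source ratios. Add that these figures assume independent patients although the Self-Management arms are delivered in groups.
3. For the Augmented CBT trial, replace the reasoning that carries the UPCC calculation over. State only that no HADS-specific calculation was possible and that 45 analysed per group detects a 0.6 SD difference on the HADS with 80% power.

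The cost is wording. No patients are added and the design does not change; the stated power becomes less favourable.

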### Setting and participants

Participants will be recruited from participating hospitals and rehabilitation centres in the Netherlands on the basis of case finding. For the Self-Management study, a minimum of 106 home-living mild stroke patients with re-integration problems and their informal caregivers on the basis of the USER-p will be recruited, through their own physicians or nurse practitioners. For the Augmented CBT study, a minimum of 106 patients who have depression and anxiety symptoms based on a cut-off score > 7 on the depression subscale of the HADS will be included. Patients will be recruited through a rehabilitation specialist, nurse practitioner or psychologist. For both studies, written informed consent for participation is obtained from both participants and their partners (if included) after recruitment.

